### Informed consent

Throughout the entire trial enrollment process, patients who have been assessed as eligible for enrollment will be introduced to the research content and specific process by trained researchers, ensuring that patients fully understand the benefits and potential risks of the trial. At the same time, patients will be informed that whether they participate or not will not affect their normal treatment and all participants' personal information will always be kept confidential. Patients will have 24 h to consider and make decisions. All participating patients must sign the informed consent.

### Randomization and allocation

Patients who meet the inclusion criteria, successfully converted to sinus rhythm and were confirmed by electrocardiogram immediately after ablation will be enrolled. Randomization will be performed after the ablation. After eligible patients sign the informed consent, baseline information will be collected, including basic information, medical history, preoperative medication history, electrocardiogram and laboratory results. Researchers will randomly allocate eligible patients at a 1:1 ratio to receive sacubitril/valsartan or not. This trial will be randomized using a dynamic stratified block group randomization method. The R package blockrand (R version 4.1.2) was used to generate a randomization table with a specified sample size, and the block sizes were randomized among 4, 6, and 8 to form the randomization pool for this trial. The trial was stratified by research centers, each of which was assigned random numbers for a block unit by “first-come, first-served”, and the random number for the next block was available in the randomization pool only when the random number for that block was used up. The process of generating the randomization table and assigning randomized numbers for this study was carried out by an independent researcher who was not involved in recruitment and subsequent interventions. After a subject had consented to participate in the trial, the recruiting physician queried the randomization number from the investigator in charge of randomization, who provided the patient's treatment allocation plan based on the participant's center and order of inclusion, as well as marked the grouping on the randomization table.

### Interventions

For all patients enrolled, if they are taking ACEI drugs, they will be given the trial drug starting 36 h after discontinuation of ACEI drugs. The control group will be given conventional perioperative medications according to guidelines of atrial fibrillation, and the trial group will receive conventional perioperative drug therapy plus sacubitril/valsartan (Beijing Novartis Pharmaceutical Company, J20171054). The test drug will be titrated according to Figure 1. The target maintenance dose is 100 mg twice per day. Based on the patient tolerance, drug dosage will be doubled every 2 weeks. If the patient cannot tolerate the maximum dose, the dose will be reduced to the maximum dose tolerated by the patient. In order to increase patient medication compliance, patients will be reminded to take drugs on time by WeChat. When patients change the dose, patients will be required to bring the packaging box of the drugs. Blood pressure, blood potassium and renal function examination will be performed at each follow-up period. If hypotension or symptomatic hypotension occurs, the dose will be adjusted.

**Figure 1 F1:**
[figure not shown]
Drug dose titration.

### Type of ablation

All patients will underwent pulmonary vein isolation (PVI) using radiofrequency energy and a three-dimensional electroanatomical mapping system (CARTO, Biosense Webster). Additional ablation lines (roof line of the LA, mitral isthmus line, or cavo-tricuspid isthmus line) or ablation of complex fractioned electrograms would not be performed during procedure for enrolling patients.. The endpoint for complex fractionated atrial electrogram ablation is a complete abatement of potentials at these sites.

### Conventional perioperative medications

Patients will be treated by standard treatment according to current guidelines (11). They will be on an uninterrupted anticoagulation regimen during the perioperative period. Uninterrupted oral anticoagulation will be taken based on stroke/thromboembolic risk during the perioperative period of AF catheter ablation for enrolling patients (9). Patients can use antiarrhythmic drugs such as Class III drugs (amiodarone) when appropriate based on the judgment of the responsible physician during the 3-month blanking period.

### Blinding

This trial is designed as an open label. Trial participants and care givers will not be blinded to the group assignment while the investigator or other relevant personnel will not be made aware of the information about the treatment subgroup to which they are assigned until the order of enrollment/randomization of the subjects has been confirmed. Data analysts and outcome evaluator will remain blinded to minimize trial bias.

### Outcome measurements

#### Primary outcome

The primary endpoint of the study will be the sinus rhythm maintenance rate within 12 months determined by at least the 24-hour Holter electrocardiogram. Patients will be given the Holter electrocardiogram at 3, 6 months and 12 months.

#### Secondary outcome

The secondary endpoint will be the sinus rhythm maintenance rate at 3 and 6 months and incidence of MACE at 3, 6, and 12 months. Cardiovascular re-hospitalization at 3, 6, and 12 months will be aggregated in HFpEF patients with AF and patients with AF and otherwise normal cardiac function. Changes in cardiac structural function indicators will be observed at 3, 6, and 12 months. Echocardiographic parameters such as LAD, LAVi, LAEF will be recorded or calculated.

#### Safety outcome

This study will also analyze the safety profile focusing on the incidence of adverse events at months 3, 6, and 12. Blood pressure will be measured and potassium and renal function will be tested during follow-up period. The main adverse events will include hypotension, hyperkalemia and renal function impairment that cannot be improved by dose reduction. Hyperkalemia (blood potassium > 5.5 mmol/L), hypotension (SBP < 90 mmHg or DBP < 60 mmHg), symptomatic hypotension (SBP ≥ 90 mmHg and dizziness, nausea, fatigue, syncope), and creatinine increase more than 50% will be considered as adverse reactions.

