### Serious adverse events

Events that are fatal, life-threatening, disabling or incapacitating, or leading to prolonged hospital stay or malformation are defined as serious adverse events in this trial.

The patient blood pressure will be observed by follow-up, and blood samples will be tested for potassium and renal function. The main adverse events will include hypotension, hyperkalemia and renal function impairment that cannot be improved by dose reduction. Adverse reaction criteria: hyperkalemia (blood potassium > 5.5 mmol/L), hypotension (SBP < 90 mmHg or DBP < 60 mmHg), symptomatic hypotension (SBP ≥ 90 mmHg and dizziness, nausea, fatigue, syncope), and creatinine increase more than 50% will be considered as adverse events.

A detailed report will be submitted to the Medicines and Healthcare Products Regulatory Agency in a timely manner when unexpected serious adverse events occur. All patients participating in the trial will receive insurance, including additional healthcare, compensation, or damages. All adverse events which may possibly related to the trial will be recorded in the CRFs.

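### The main adverse events carry a dose-reduction qualifier that the protocol defines only for the sacubitril/valsartan arm, beside arm-neutral thresholds, and nothing says which of the two is counted

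*Protocol article*

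**What the plan says.** All references are to the protocol article.

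- **Qualified rule.** Safety outcome names as main adverse events "hypotension, hyperkalemia and renal function impairment that cannot be improved by dose reduction". Serious adverse events repeats the sentence.
- **Thresholds.** The next sentence in Safety outcome sets numeric criteria with no dose condition: "Hyperkalemia (blood potassium > 5.5 mmol/L), hypotension (SBP < 90 mmHg or DBP < 60 mmHg", then symptomatic hypotension and a creatinine rise. Serious adverse events gives the same criteria.
- **Labels.** In Safety outcome the sentence ends "creatinine increase more than 50% will be considered as adverse reactions". In Serious adverse events it ends "creatinine increase more than 50% will be considered as adverse events".
- **Symptomatic hypotension.** Both sections define it as "symptomatic hypotension (SBP ≥ 90 mmHg and dizziness, nausea, fatigue, syncope", with no upper pressure limit and no required fall.
- **Dose changes.** Interventions describes titration for the test drug only; controls receive conventional medication. The same paragraph says: "If hypotension or symptomatic hypotension occurs, the dose will be adjusted".
- **SAE definition.** Serious adverse events lists fatal, life-threatening and disabling events, and ends the list with "or leading to prolonged hospital stay or malformation". New hospital admission is not named.
- **Use.** Safety outcome plans to analyse adverse event incidence at months 3, 6 and 12. Blinding leaves participants and caregivers aware of the allocation.

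**The concern.** A between-arm safety comparison needs one event definition that can be applied in the same way to every patient. Here one of two adjacent definitions depends on what happens after a dose reduction, a step that the protocol sets out for one arm only. In the trial arm, an event that improves after down-titration may leave the count. For a control patient the text gives no way to decide whether the condition is met. An analyst could count all control events, none, or some, and each choice gives a different risk difference.

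Two related wordings affect the same safety summary. Symptomatic hypotension is reached through symptoms at an SBP of 90 mmHg or above, so nothing in it marks low pressure, and the symptoms come from patients who know their treatment. The SAE sentence covers a prolonged stay but not a new admission, in a trial whose follow-up is mainly outpatient.

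**Working it through.** The article gives no expected safety rates, so there is no stated figure to reproduce. The check is a comparison of the text, followed by an illustration with assumed rates.

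**1. Can each rule be applied in both arms?**

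| Rule | Trial arm | Control arm |
|---|---|---|
| Main adverse events with the dose-reduction qualifier | Applicable; events that improve after down-titration can drop out | No study dose to reduce; meaning undefined |
| Thresholds for potassium, blood pressure, creatinine | Applicable | Applicable in the same way |

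Interventions itself prescribes dose adjustment on hypotension, so the situation addressed by the qualifier will arise in the trial arm by design. The grammar adds a further doubt: the qualifier may cover all three events or only renal impairment.

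**2. What can the qualifier do to the risk difference?**

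Assumed inputs, none from the article:

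- pT, true trial-arm risk of a threshold event: 10%, 15%, 20%
- pC, true control risk: 10%
- f, share of trial-arm events that improve on dose reduction: 0% to 75%

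Formulas (trial minus control):

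- Arm-neutral thresholds: pT - pC
- Qualifier, all control events counted: pT × (1 - f) - pC
- Qualifier, no control event countable: pT × (1 - f) - 0

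With pT = 15%, pC = 10%, f = 50%:

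- Arm-neutral: 15 - 10 = +5.0 points
- All control events counted: 15 × 0.5 - 10 = 7.5 - 10 = -2.5 points
- No control event counted: 15 × 0.5 - 0 = +7.5 points

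Over the whole assumed grid:

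| Counting rule | Lowest | Highest |
|---|---|---|
| Arm-neutral | 10 - 10 = 0 | 20 - 10 = +10 |
| Qualified, all controls counted | 10 × 0.25 - 10 = -7.5 | 20 × 1 - 10 = +10 |
| Qualified, no control countable | 10 × 0.25 = +2.5 | 20 × 1 = +20 |

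The choice of rule can change the size and the sign of the difference, and the text does not fix the direction. If the qualifier covers renal impairment alone, the same arithmetic applies to that component only.

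**3. Symptomatic hypotension.** The criterion has a lower SBP bound and no upper one. If the comma-separated symptoms are read as any one of them, fatigue at a normal or raised pressure qualifies. The wording is the same for both arms, so this is a fault of specificity. It can bias the comparison only through open-label symptom reporting, which the blinded outcome evaluator described under Blinding cannot undo.

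**4. SAE definition.** A non-life-threatening admission for hyperkalaemia or renal impairment in an outpatient meets none of the listed SAE criteria. Follow-up asks about rehospitalization, but the causes listed under Definition are all cardiovascular, so such an admission has no clear place there. Withdrawal criteria removes patients who have serious adverse events, so adding admission to the SAE definition would also widen withdrawal unless the two sections are reconciled.

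**The case against.** The strongest reply is that the arm-neutral thresholds already are the working definition. They are printed in both sections. The sentence on main adverse events says that these will include the named events, which is not exclusive. Follow-up lists hypotension, high potassium and renal impairment for assessment with no dose condition. No sentence says that an event improving after down-titration is deleted. This is also a condensed article, and the safety summary carries no stated hypothesis test.

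Most of this stands, and it limits the point. It does not remove it: the qualified sentence is printed twice, and nothing says that the thresholds override it.

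A reader might infer more than the documents support:

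- **That the safety definitions as a whole are not comparable between arms.** The thresholds are comparable; the defect is a second, unreconciled rule.
- **That a qualified event cannot exist among controls.** Background drugs might be reduced, and the qualifier may attach only to renal impairment. The accurate statement is that its meaning for controls is undefined.
- **That the trial arm's count is biased downward.** That holds only if control events are all counted; if none can be, the difference moves the other way.
- **That symptomatic hypotension loses events at low pressure.** Syncope with SBP below 90 mmHg already meets the hypotension threshold.
- **That the data monitoring committee would miss new admissions.** Rehospitalization is asked about at each follow-up, cardiovascular re-hospitalization is a secondary outcome, the CRF holds hospitalization records, and the committee reviews safety. All that can be said is that the SAE route may not flag some admissions.

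**Conclusion.** The point holds as an unreconciled pair of counting rules, one arm-dependent and one arm-neutral, for the main safety comparison. In the assumed example, the neutral +5.0 points can be reported as -2.5 or +7.5. These figures rest on assumed risks and an assumed share of events improving; they show that sign and size are open, not what this trial will find. If the thresholds are in fact what is counted, the distortion is nil and only the text needs repair.

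The lack of a low-pressure criterion in symptomatic hypotension and the omission of new admission from the SAE sentence are real but smaller. Neither is a difference in definition between arms. The primary endpoint and sample size are unaffected. The correction is worth making now, because the trial was still recruiting when the article appeared and the definitions govern how later events are classified.

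**What to change.** 1. For the between-arm comparison, count every event that meets the stated numeric thresholds for potassium, blood pressure and creatinine, identically in both arms, whatever follows a dose change.
2. Report improvement after dose reduction only as a descriptive column.
3. Use one label, adverse event, in Safety outcome and Serious adverse events.
4. Tabulate symptomatic hypotension apart from measured hypotension, with the recorded pressure, and say whether one listed symptom suffices. This concerns tabulation only; the dose-adjustment trigger in Interventions stays untouched.
5. Include new hospital admission in the SAE definition for reporting, and reconcile it with Withdrawal criteria so that the effect on withdrawal is stated and not left to follow by default.

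The cost is wording in two sections, a cross-check against Withdrawal criteria, table shells and somewhat more SAE reports. The change goes through the amendment route under Auditing and amendment. No dose rule or sample size changes.

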### Definition

This study differentiate different cardiovascular causes for re-hospitalization into cardioversion, repeat ablation, heart failure, acute coronary syndrome, stroke or transient ischemic attack, or other cardiovascular-related diseases.

MACE are defined as heart failure, myocardial infarction, stroke, malignant arrhythmia and cardiac death. The specific definitions are as follows:
(1)Definition of heart failure: patients who had a history of HF-plausible symptoms, physical examination changes, electrocardiogram changes, cardiac ultrasound changes, and elevated serological markers of heart failure (NT-proBNP > 125 pg/ml or BNP ≥ 35 pg/ml) will be clinically diagnosed as heart failure according to the 2022 AHA/ACC/HFSA Guidelines: Management of Heart Failure. Heart failure with reduced ejection fraction (HFrEF) is classified as an LVEF ≤ 40% (17).(2)Definition of acute coronary syndrome: includes ST-segment elevation myocardial infarction (STEMI), non-ST-segment elevation myocardial infarction (NSTEMI), and unstable angina (UA) according to the guidelines for rapid diagnosis and treatment of acute coronary syndromes in emergency medicine (18).(3)The diagnosis of malignant arrhythmia (MA) refers to the diagnostic criteria for malignant arrhythmia in the 2020 American Heart Association Guidelines for Resuscitation and Emergency Cardiovascular Care (19). MA includes ventricular arrhythmias (ventricular tachycardia and ventricular fibrillation) and grade II or III atrioventricular block. Each type of MA may occur alone or in combination with other types at the same time.

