### Study hypothesis and objectives

The overall expectation is that patients taking sacubitril/valsartan with persistent atrial fibrillation after catheter ablation will have better sinus rhythm maintenance and cardiovascular outcomes within 12 months than those not taking. This prediction will be tested with the following three objectives. The primary objective will be to evaluate the efficacy of sacubitril/valsartan on sinus rhythm maintenance after ablation of persistent AF patients in this trial. Whether sacubitril/valsartan decreases the incidence of MACE and improves structural indices of the atrium in patients with AF is the secondary objective of this study. The third objective will be to determine the efficacy of sacubitril/valsartan on re-hospitalization rates for cardiovascular causes.

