### Statistical and analytical plans

The statistical analysis will be along with the intention-to-treat (ITT) principles. The ITT population will include patients who meet the criteria, are randomized, and take at least one dose of drugs after being enrolled. For statistical description, continuous variables are described by using mean and standard deviation if they satisfy a normal distribution, skewed distributions are described by medians and quartiles, while categorical variables will be presented as frequency or percentage in each category. For the baselines, the t-test is used to compare the differences for quantitative variable if the data meets the normality test, otherwise, the data will be transformed or rank sum test. Categorical variables such as disease history and smoking history can be tested using chi-square test or rank sum test. For outcomes such as 239sinus rhythm maintenance rate, all-cause death, re-hospitalization rate for cardiovascular causes and MACE, Kaplan-Meier curves will be used to characterize how the probability of an endpoint event changes with survival time, and comparisons between survival curves will be carried out using log-rank tests. We used cox proportional hazards models to estimate hazard ratios and 95% confidence intervals. Cardiac structural function indicators will be described by mean value (±SD) or median and quartiles, and the sphericity of the covariance array will be tested by the Mauchly method. If the data satisfies the sphericity of the covariance array, the analysis of variance with repeated measures data will be used for group comparisons of each indicator. If it is not satisfied, the Greenhouse-Geisser method will be used for comparison of differences. Missing observations will be accounted for using the predictive mean matching (PMM) method. If the missing data is numerical, it will be filled by predictive mean matching; meanwhile if the missing data is non-numerical, logistic regression and discriminant functions will be used to fill it. The *p*-value threshold is 0.05(*p* < 0.05), and when it is below this threshold, indicating that the difference is statistical significant. SPSS statistical software (SPSS Inc, Chicago, IL, USA, version 23) will be used to analyse data.

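### The single cardiovascular re-hospitalization test counts admissions for cardioversion and repeat ablation, so a positive result would not show whether other cardiovascular admissions fell; a cause-split analysis is a cheap improvement

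*Protocol article*

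**What the plan says.** All references are to the protocol article.

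- **Study hypothesis and objectives.** Rhythm is the primary objective. Re-hospitalization stands apart from it: "The third objective will be to determine the efficacy of sacubitril/valsartan on re-hospitalization rates for cardiovascular causes".
- **Definition.** The causes are listed and told apart: the study is to differentiate "different cardiovascular causes for re-hospitalization into cardioversion, repeat ablation, heart failure, acute coronary syndrome", followed by stroke or TIA and other cardiovascular disease.
- **Secondary outcome.** "Cardiovascular re-hospitalization at 3, 6, and 12 months will be aggregated in HFpEF patients with AF" and in patients with otherwise normal cardiac function. This describes patient groups, not causes of admission.
- **Statistical and analytical plans.** The outcome is analysed as one rate: for "re-hospitalization rate for cardiovascular causes and MACE, Kaplan-Meier curves will be used", with log-rank tests and Cox models. No analysis by cause is stated.
- **Blinding.** "Trial participants and care givers will not be blinded to the group assignment". In addition, "Data analysts and outcome evaluator will remain blinded to minimize trial bias".
- **Primary outcome.** Sinus rhythm maintenance within 12 months.

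**The concern.** Heart failure, coronary and stroke admissions are driven mainly by acute illness. An admission for cardioversion or repeat ablation is different in two ways.

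First, it is a treatment for lost sinus rhythm, so it can occur only after the event that the primary endpoint already counts. If the drug preserves rhythm, the re-hospitalization rate falls for that reason alone. The third objective then partly repeats the first.

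Second, it is discretionary, and those who decide know the allocation. If recurrences in the control arm are sent for a procedure more readily than recurrences in the drug arm, the endpoint favours the drug even when rhythm does not differ. A blinded evaluator can classify the cause of an admission afterwards but cannot undo a decision to admit that depended on the arm.

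At stake is how a positive result is read. As planned, the test cannot separate fewer rhythm procedures from fewer other cardiovascular admissions.

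**Working it through.** **The plan's own figures.** The article gives no rate, effect or power for re-hospitalization, so nothing can be reproduced for this endpoint. The recurrence inputs in the Sample size section can be checked: 42% falling by 20 points to 22% gives ln(0.78)/ln(0.58) = 0.456, which matches the stated 0.46.

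**Inputs from the documents.** Control recurrence is 42% at 12 months. There are 231 patients per arm, or 231 × 0.8 ≈ 185 after the planned 20% missing visits.

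**Assumptions, not in the documents.** q is the share of recurrences admitted for cardioversion or repeat ablation. b is the 12-month risk of any other cardiovascular admission, equal in both arms, taken as 5%, 8% or 12%. The test is two-sided at 0.05, so the nominal chance of a false benefit is 2.5%.

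**Formulas.**
- Risk per arm: p = 1 − (1 − recurrence × q)(1 − b)
- HR = ln(1 − p1)/ln(1 − p0), with 1 = drug and 0 = control
- Chance of significance in the drug's favour = Φ(½ × √events × |ln HR| − 1.96), with events = n per arm × (p0 + p1)

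**Case A: no drug effect on rhythm or on other admissions, only a different procedure threshold.** Recurrence is 42% in both arms and control q = 50%.

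Worked example with drug q = 35%, b = 5% and 231 per arm:
- p0 = 1 − 0.79 × 0.95 = 0.2495
- p1 = 1 − 0.853 × 0.95 = 0.1897
- HR = ln(0.8103)/ln(0.7505) = 0.733
- events = 231 × (0.2495 + 0.1897) ≈ 101.4
- Φ(½ × √101.4 × 0.311 − 1.96) = Φ(−0.394) = 0.347

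Over b = 5–12% and 185–231 per arm:

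| Drug-arm q | Gap | HR | Chance of false benefit |
|---|---|---|---|
| 45% | 5 points | 0.91–0.93 | 5.8–7.3% |
| 40% | 10 points | 0.82–0.86 | 12.1–17.5% |
| 35% | 15 points | 0.73–0.79 | 22.4–34.7% |

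**Case B: the planned rhythm effect (42% vs 22%), the same procedure threshold in both arms, no effect on other admissions.** With q = 20–50%, the same b and 185–231 per arm, HR is 0.58–0.80 and the chance of significance is 14–74%. This is a true effect on the endpoint as defined, not a false positive. It shows only that the total can move while non-procedural admissions do not.

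**After the split.** An endpoint without the procedural admissions has equal risk b in both arms in either case, so HR = 1 and the chance of a false benefit returns to 2.5%.

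**The case against.** The strongest reply is that the endpoint measures what it promises. The objective concerns cardiovascular re-hospitalization in general, and an admission for cardioversion or repeat ablation is one. Avoiding such admissions matters to these patients, and overlap between a secondary and the primary endpoint is not an error. This stands. It rules out calling the definition wrong, and it is why the total should be kept.

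A reader might infer that the plan pools the causes without distinguishing them. It does not: the Definition section differentiates them, and an analysis plan that is not shown may report them by type. What remains is that the one test the article states for this endpoint uses the undivided rate.

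A reader might also infer that the trial has no test of non-rhythm events. It does: MACE (heart failure, myocardial infarction, stroke, malignant arrhythmia, cardiac death) contains neither procedure and has its own Kaplan-Meier, log-rank and Cox analysis. It only partly answers the question, because it is not limited to admissions and does not list unstable angina, TIA or other cardiovascular admissions.

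Finally, Case A rests on an assumed gap in procedure thresholds. Nothing in the documents supports its size or its direction, and at a 5-point gap the inflation is small. The table is therefore a sensitivity range, not a prediction that a false benefit is likely.

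**Conclusion.** The point holds as a minor, inexpensive improvement to a secondary endpoint. The stated test mixes admissions that follow primary-endpoint failure, decided without blinding, with other cardiovascular admissions. A positive result would leave open which of these fell and whether procedure thresholds differed by arm.

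These conclusions follow from the definition and the open-label design. Their size does not: the Case A range, from 5.8% to 34.7% against 2.5%, depends on the assumed q, its gap between arms, and b. The documents do not support a claim that the endpoint is invalid, that the passages contradict each other, or that a stated figure is wrong.

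**What to change.** Keep total cardiovascular re-hospitalization as planned. In the Statistical and analytical plans section:

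1. Add a pre-specified Kaplan-Meier, log-rank and Cox analysis of first cardiovascular re-hospitalization, excluding admissions made only to perform cardioversion or repeat ablation.
2. Report those procedural admissions separately by arm.
3. State that any claim of fewer cardiovascular admissions beyond rhythm procedures rests on the non-procedural analysis.

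The cost is a few sentences and one more secondary analysis with fewer events than the total. No new data are needed, because the cause of admission is already classified, and the article reports that recruitment is under way, so the change can precede the final analysis. The split reduces open-label bias but does not remove it, since unblinded care givers also take part in decisions to admit for heart failure or other cardiovascular disease.
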